#### Follow-up

Follow-up observations will be conducted before the trials, once every 2 weeks during the treatment, and 2 months after the last treatment.

### Statistical analysis

Statistical analysis will be performed by using the software program Statistical Package for the Social Sciences (SPSS 15.0, Chicago, IL, USA). Participants’ demographic information and levels of major measured variables were analyzed by descriptive statistics. Means and standard deviations of the clinical indices will be calculated, after which the evaluation between the two groups will be compared using a Student’s *t*-test. The difference of evaluation scores before and after each examination point will be analyzed using paired *t*-tests. The repeated measures analysis of variance (ANOVA) will be used to analyze longitudinal and repeated measured data for the clinical indices across the 8 data collection points (treatments for 16 weeks, followed-up evaluation biweekly). A value of *P* < 0.05 will be regarded as statistically significant for the above statistical analyses.

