### Study design

This study proposes a patient-assessor-blinded, randomized, sham-controlled crossover trial with a 2-week washout period between each crossover phase. The trials will be conducted at the Chiayi Chang Gung Memorial Hospital. This study will adhere to the recommendations of the Consolidated Standards of Reporting Trials (CONSORT) [13] to allow for greater completeness, transparency and accuracy of reporting. The protocol for this study has been registered in the Clinical Trials register (ClinicalTrials.gov Identifier: NCT02167308).

Subjects who voluntarily sign a consent form will undergo the trial according to the study design. When a subject is determined to be fit for participation based on inclusion and exclusion criteria, the subject will be randomly assigned to 1 of 2 groups in a ratio of 1:1. One group is the true laser experimental group and the other is the sham laser control group. Each group will receive their treatment 3 times a week for 8 weeks. After 8 weeks of treatment and a 2-week washout period, the control group will switch to the experimental group while the experimental group will switch to the control group. The subjects then undergo the treatment of their new group for another 8 weeks (Fig. 1).

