### Sample size

This study is a pilot study for evaluating the efficacy of actual laser acupuncture compared to sham laser acupuncture, and to evaluate the feasibility of large clinical trials. In the hopes of decreasing the subject drop-out rate, the trial is designed to only last 8 weeks. Assuming a drop-out rate of 10%, the desired sample size for this pilot study is 104 subjects, with 52 in each group. Based on the *a priori* calculation in G*Power 3.1.3 [14] it was determined that a minimum total sample size of 92 would be needed in a repeated measures between factors design to show a significant difference (effect size = 0.25; α = 0.05; 1 – β = 0.8; number of measurements = 8; correlation among repeated measures = 0.2).

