#### Outcome assessment

Before the treatment, clinical assessment parameters will be evaluated by an evaluator. Post-treatment assessments will be evaluated by a different evaluator. The physician who applies the treatment to the subject will not be involved in assessing the parameters. This way, the subject and both evaluators will be blinded to the treatment being performed.

The primary outcome measurement is the BMI change from baseline. BMI will be calculated using weight (kg)/height (m^2^). Secondary outcome measurements include waist circumference, hip circumference, WHR, body fat percentage, hunger and a Short-Form 36-item Health Survey (SF-36). Waist circumference will be measured at the midpoint between the lower margin of the least palpable rib and the top of the iliac crest, using a stretch‐resistant tape. Hip circumference will be measured around the widest portion of the buttocks, with the tape parallel to the floor [18]. Bioelectrical impedance will be used to measure the percentage of body fat.

For hunger, a Visual Analog Scale (VAS) with horizontal lines will be used, graded from 0 mm, representing no hunger, to 100 mm, representing the most extreme hunger imaginable. Subjects will be asked to mark their level of hunger on the VAS. Subjects will be prohibited from accessing their previous VAS records on subsequent sessions. Measurements of appetite as expressed by ratings on the VAS has been shown to be highly reproducible and reliable for appetite research [19]. These clinical assessments will be performed before the trials, once every 2 weeks during the treatment, and 2 months after the last treatment.

SF-36 is a widely used questionnaire for measuring self-reported physical and mental health status. Each subject will answer the SF-36 questionnaire before the trials, immediately after the trials and 2 months after the last treatment. The SF-36 questionnaire consists of 11 questions concerning general health, and can be divided into two aggregate summary measures: the Physical Component Summary and the Mental Component Summary. The SF-36 has become one of the most widely used measures to evaluate health-related quality of life [20].

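### The between-group t-test uses no baseline term and is not tied to the primary outcome, BMI change from baseline; how much precision this costs depends on whether raw values or changes are tested

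*Protocol article*

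**What the plan says.** All references are to the protocol article.

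- **Statistical analysis, between groups:** "Means and standard deviations of the clinical indices will be calculated, after which the evaluation between the two groups will be compared" with a Student's t-test. No covariate is named, and raw values or changes are not specified.
- **Statistical analysis, within group:** "The difference of evaluation scores before and after each examination point will be analyzed using paired" t-tests.
- **Statistical analysis, longitudinal:** a repeated measures ANOVA "will be used to analyze longitudinal and repeated measured data for the clinical indices across the 8 data collection points". The section does not say whether the pre-treatment value is one of the eight points, or which ANOVA effect estimates the treatment difference.
- **Outcome assessment:** "The primary outcome measurement is the BMI change from baseline". Waist, hip, waist-to-hip ratio, body fat percentage, hunger and SF-36 are listed as secondary outcomes without being defined as changes.
- **Outcome assessment, timing:** "These clinical assessments will be performed before the trials, once every 2 weeks during the treatment, and 2 months after the last treatment". SF-36 has its own schedule, which also includes a pre-trial administration.
- **Study design:** "the subject will be randomly assigned to 1 of 2 groups in a ratio of 1:1", and after a 2-week washout "the control group will switch to the experimental group while the experimental group will switch to the control group".

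**The concern.** Eligibility is any BMI over 25 kg/m², with no upper limit, so much of the variation in a post-treatment BMI is likely to be the subject's starting BMI. A two-sample t-test on post-treatment values leaves all of that variation in the error term. A chance difference in starting BMI between the groups then passes directly into the estimate. The starting value is measured but is not used in this comparison.

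The order of the sentences invites this reading: the indices go to the between-group test, and before/after differences go separately to the paired tests. No sentence in the analysis section says that the between-group test is on change, which is how the primary outcome is defined. For the secondary outcomes, the Outcome assessment section does not supply even that definition.

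At stake are the precision of the main comparison and a clear link between the primary outcome and the test applied to it.

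**Working it through.** **Inputs from the protocol article (Sample size):** minimum total 92, so 46 per group; 104 enrolled after 10% drop-out; α = 0.05; power 0.80; "effect size = 0.25", taken as Cohen's f, so d = 0.5 for two groups; 8 measurements; correlation among repeated measures 0.2.

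**Assumed, because the article does not give them:** two-sided t-test; equal SD before and after treatment; the baseline-to-post correlation r; the SD of BMI.

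**The plan's own figure.** The drop-out step is consistent: 92/0.9 = 102.2, so 103, or 104 for equal groups. The 92 itself does not come back. For a repeated measures between-factors test, λ = f²·N·m/(1+(m−1)ρ). With f = 0.25, m = 8, ρ = 0.2 and two groups, N = 40 gives λ = 0.0625·40·8/2.4 = 8.33 and power 0.803; N = 92 gives λ = 19.17 and power 0.991. That is a separate matter. Here 92 serves only as the planned number of completers.

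**Step 1: variance of the three analyses, relative to a raw post-treatment value.**
- raw t-test: 1
- t-test on change: 2(1−r)
- baseline-adjusted model: 1−r²
- adjusted relative to change: (1−r²)/[2(1−r)] = (1+r)/2

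**Step 2: detectable difference.** With 46 per group, two-sided α = 0.05 and power 0.80 (noncentral t), the raw t-test detects 0.590 SD. The other two analyses multiply this by the square root of their variance.

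| assumed r | raw (SD) | change (SD) | adjusted (SD) | adjusted/change variance |
|---|---|---|---|---|
| 0.5 | 0.590 | 0.590 × √1.00 = 0.590 | 0.590 × √0.75 = 0.511 | 0.75 |
| 0.7 | 0.590 | 0.590 × √0.60 = 0.457 | 0.590 × √0.51 = 0.422 | 0.85 |
| 0.9 | 0.590 | 0.590 × √0.20 = 0.264 | 0.590 × √0.19 = 0.257 | 0.95 |

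**Step 3: power at d = 0.5, 46 per group (raw / change / adjusted).**
- r = 0.2, borrowing the correlation from the sample size section: 0.66 / 0.47 / 0.68
- r = 0.5: 0.66 / 0.66 / 0.78
- r = 0.8: 0.66 / 0.96 / 0.98
- r = 0.9: 0.66 / above 0.99 / above 0.99

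A change score can therefore do worse than raw values when r is low. The adjusted model is at least as precise as either in every row.

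**Step 4: BMI units, illustration only.** Assume an SD of 3 to 5 kg/m² and an effect of 0.5 kg/m². Power for raw values is 0.12 to 0.08. At r = 0.9 it is 0.42 to 0.19 for change and 0.44 to 0.19 adjusted. At r = 0.98 it is 0.98 to 0.66 for both. For r from 0.9 to 0.98, adjustment adds at most 0.02 over change.

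**Step 5: fit to the design.** Steps 1 to 4 compare two separate groups of 46. In this trial each subject is due to receive both laser and sham. A within-subject comparison removes the stable subject level by itself, so in a crossover model with a subject effect a pre-trial covariate adds little to the laser-minus-sham contrast. There the gain comes from making the comparison within subject and including a period term, neither of which the analysis section describes.

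**The case against.** A reader might infer that the plan tests raw BMI, so that between-subject spread swamps the treatment effect and the loss is 0.59 against 0.26 SD. The article does not support that as a statement of fact. The analysis sentence leaves raw or change open, and the Outcome assessment section defines the primary outcome as a change. Reading the two together as a t-test on BMI change is natural, and on that reading the stable BMI level cancels. At r = 0.9 the detectable differences are then 0.264 and 0.257 SD, about 3% apart. The article gives no BMI SD, no effect in kg/m² and no baseline-to-post correlation from which swamping could be shown. This part of the objection stands.

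It is also fair that an unadjusted comparison is valid under randomisation. Chance imbalance is reflected in the standard error and is not bias, so the issue is efficiency and clarity. That stands too.

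Two further objections bear on the remedy. The parallel-group magnitudes do not carry over to a crossover model. And the listed assessments do not name an end-of-washout visit, so a period-2 baseline cannot be taken as available. Both are right and shape the fix.

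The argument that covariate choice can be left to a fuller plan carries less weight. The article does not merely omit a model: it fixes a specific test, and a better one is available with the pre-trial data it already collects. The paired tests and the repeated measures ANOVA do not clearly repair this. The first are described as before/after contrasts, and for the second the role of baseline and the treatment effect of interest are unstated.

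**Conclusion.** The point holds in a conditional form. The plan fixes an unadjusted two-group t-test, makes no use of the baseline in it, and does not connect it to the primary outcome as defined.

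- **If raw post-treatment values are tested:** most of the precision is lost, 0.59 SD detectable against 0.26 SD with adjustment at r = 0.9 (0.42 SD at r = 0.7).
- **If changes are tested:** adjustment makes little difference for BMI (variance factor 0.95 at r = 0.9) and a material one for less stable outcomes such as hunger or SF-36 (0.75 at r = 0.5).

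All of this rests on assumed correlations, equal SDs and a parallel comparison of 46 per group. It shows what is lost if the t-test is used as the group comparison. It does not measure what a baseline covariate would add to a properly specified crossover model. The change is worth making because the plan should say which quantity is compared, and because baseline adjustment is no less precise than either reading over the range checked.

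**What to change.** In the Statistical analysis section:

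1. Replace the between-group Student's t-test with a linear model of the end-of-treatment value, with treatment and the pre-treatment value of the same outcome as covariate. For BMI this gives the same treatment contrast whether the response is written as the final value or as the change, so it agrees with the primary outcome definition.
2. For the two-period crossover, estimate laser minus sham within subject in a mixed model with treatment, period, sequence and a random subject effect.
3. Use a period-2 baseline only if an end-of-washout assessment is actually made, and note that it may carry over a period-1 effect.
4. Report the adjusted difference with a 95% CI.

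The cost is a short change to the analysis text and a little more analysis work. The pre-trial values are already collected, so items 1 and 2 need no new measurement.

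### The repeated-measures ANOVA over both crossover periods names no treatment term, which leaves the laser effect in a 7-df interaction; if uncorrected, that test would have about 10% to 12% type I error under strong serial correlation

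*Protocol article*

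**What the plan says.** The Statistical analysis section of the protocol article lists several analyses. Group means are to be compared by a t-test ("after which the evaluation between the two groups will be compared using a Student’s" *t*-test), and before-after differences by paired t-tests. A repeated-measures ANOVA "will be used to analyze longitudinal and repeated measured data for the clinical indices across the 8 data collection points". A bracket in that sentence describes the points as biweekly over 16 weeks of treatment, that is, four per 8-week period and two periods. One rule covers everything: P "< 0.05 will be regarded as statistically significant for the above statistical analyses". The software is "Statistical Package for the Social Sciences (SPSS 15.0, Chicago, IL, USA").

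Under Study design, each subject has 8 weeks of one treatment, a 2-week washout and 8 weeks of the other. The primary outcome, under Outcome assessment, is change in BMI from baseline.

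The Sample size section plans on an ANOVA of the between-subject kind: a "minimum total sample size of 92 would be needed in a repeated measures between factors design", with "1 – β = 0.8; number of measurements = 8; correlation among repeated measures = 0.2". It then allows for drop-out: "Assuming a drop-out rate of 10%, the desired sample size for this pilot study is 104 subjects, with 52 in each group".

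The article does not define the factors of the ANOVA or say which term tests the laser. It does not say whether the test is univariate or multivariate, or whether a sphericity correction applies.

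**The concern.** In a parallel-group trial, a group factor crossed with visit gives a usable group main effect. Here it does not. Over the 8 points, both groups have had laser for half the visits and sham for the other half, so the group main effect compares two averages of the same mixture. In the layout that the text suggests, what remains is the group-by-visit interaction.

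That interaction is a poor place for the main question. It has 7 degrees of freedom, so it does not isolate laser against sham. Its univariate F test is valid only under sphericity, and BMI readings 2 weeks apart can be expected to agree more closely than readings 16 weeks apart, which is the pattern that breaks sphericity. A standard repeated-measures ANOVA also uses only subjects with a complete series. Someone who leaves in the second period therefore contributes nothing, not even the first-period readings.

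At stake are a test that does not address the treatment contrast directly, a possible excess of false positives, and the loss of data already collected.

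**Working it through.** **The plan's own figure.** The minimum of 92 comes from a between-factors test with f = 0.25, m = 8 and correlation 0.2. The usual formula is λ = f²·N·m / (1 + (m − 1)ρ), with 1 and N − 2 degrees of freedom.
- N = 40: λ = 0.0625 × 40 × 8 / 2.4 = 8.33, power 80.3%.
- N = 92: λ = 19.17, power 99.1%.

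So 92 is not reproduced. The drop-out step is: 92 / 0.9 = 102.2, hence 103, or 104 in two equal groups. The failure to reproduce 92 is a separate matter and does not enter the results below. What matters here is that the between-factors test is the term from which the laser effect cancels.

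**Where the laser effect sits.** Suppose laser shifts BMI by δ at the four visits of its period, with no carry-over.
- Laser-first group, mean over 8 visits: (4δ + 0) / 8 = δ/2.
- Sham-first group, mean over 8 visits: (0 + 4δ) / 8 = δ/2.
- Difference in the group main effect: 0.
- Difference by visit: +δ at visits 1 to 4, −δ at visits 5 to 8, which is pure group-by-visit interaction.

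The same cancellation holds if the effect builds up over a period, provided it builds up alike in both. Carry-over or a treatment-by-period interaction would make it inexact.

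**Type I error of the uncorrected interaction test.** Inputs from the protocol are 92 subjects in two equal groups, 8 visits and α = 0.05. Visits are placed at weeks 2, 4, 6, 8, 12, 14, 16 and 18, from the 8-week periods and the 2-week washout. The covariance is assumed.

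The test has 7 and 7 × 90 = 630 degrees of freedom, with critical value 2.02. Let λ₁ to λ₇ be the eigenvalues of the covariance after removing the subject mean. Under no effect, the F ratio is distributed as [Σλᵢχ²₁ / 7] / [Σλᵢχ²₉₀ / 630], and ε = (Σλᵢ)² / (7Σλᵢ²). With 400,000 draws per setting:

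| Covariance of the 8 values | ε | Uncorrected |
|---|---|---|
| Common correlation 0.2 (the protocol's), raw BMI | 1.00 | 5.0% |
| Autoregressive 0.2 per 2 weeks | 0.95 | 5.3% |
| Autoregressive 0.5 | 0.72 | 7.1% |
| Autoregressive 0.8 | 0.44 | 9.8% |
| Autoregressive 0.9 | 0.37 | 10.8% |
| Autoregressive 0.97 | 0.32 | 11.5% |
| Random slope (intercept SD 3, slope SD 0.05 per week, residual SD 0.2) | 0.26 | 12.5% |
| Common correlation 0.2, change from each period's own baseline | 0.56 | 8.3% |

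Other random-slope settings run from 6.7% to 14.9%. The upper bound, at ε = 1/7, is 15.8%. With Greenhouse-Geisser degrees of freedom (7ε and 630ε, true ε), every setting tried gives 4.8% to 5.1%.

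The last row of the table matters because the primary outcome is a change from baseline. If each period's change uses that period's baseline, the shared baseline alone breaks sphericity, even under the protocol's own correlation.

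**Tests that keep their level.** Under autoregressive correlation 0.9, the group main effect rejects 4.8% of the time under no effect. A 1-df contrast of treatment (first-period mean minus second-period mean, compared between sequences) rejects 5.0% of the time.

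**Complete series.** With 10% drop-out, 104 × 0.1 ≈ 10 subjects would be left out of the ANOVA altogether, whatever they had contributed before leaving.

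**The case against.** A reader might infer that the trial's test of laser will reject about twice as often as stated. The article does not support that, for three reasons.

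- It never says that the test is uncorrected. A Greenhouse-Geisser or multivariate test fits its wording and is available in SPSS. In a condensed article whose analysis plan is not shown, leaving out the correction is no error. This stands: any inflation has to be stated as conditional.
- The inflation depends on a covariance that the article does not give. Its only correlation, a common 0.2, gives 5.0% on raw BMI. High correlation by itself does not break sphericity; the decay with time does. This also stands, which is why a range is given.
- The 7-df interaction is not fixed as the laser test. A treatment-by-visit layout would give a 1-df treatment test free of sphericity, the Student's t-test needs no sphericity, and the ANOVA is not named as primary. This stands in part. The text describes one run of 8 points across both periods and names no treatment contrast, and its two-group t-test is not described as a within-subject comparison.

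A reader might also infer heavy loss of subjects from scattered missed visits. The article gives no missed-visit rate, so only the 10% drop-out can be used. The sample size is already inflated for drop-out, but that restores numbers; it does not recover the partial data that the ANOVA discards.

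**Conclusion.** The point holds as a criticism of a stated method. The repeated-measures ANOVA across both periods, as described, does not isolate laser against sham. Its group main effect largely cancels the treatment effect, and with one 8-level time factor the effect is left in a 7-df interaction that needs sphericity if tested by the univariate F.

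If that F were uncorrected, type I error would be about 10% to 12% under autoregressive correlation of 0.8 to 0.97 per 2 weeks, and about 5% to 15% across plausible covariances. These figures rest on an assumed covariance and on 46 subjects per sequence. The structural part, that the planned ANOVA has no treatment term and drops incomplete subjects, needs no assumption about covariance. The change is worth making even in a pilot, because it is cheap and can be made before analysis.

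**What to change.** For the laser-versus-sham comparison, replace the repeated-measures ANOVA by a linear mixed model:

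- fixed effects for treatment, period, sequence, visit within period and period baseline;
- subject effects, with an unstructured or autoregressive covariance within period;
- small-sample degrees of freedom;
- all available readings, including those of subjects who leave early.

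Apply the P < 0.05 rule for laser against sham to the treatment term. This term isolates the contrast, the model does not require sphericity, and first-period data from drop-outs are kept. If the ANOVA is retained as a supporting analysis, say that its P comes from the Greenhouse-Geisser-corrected result.

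The cost is a change of wording and slightly more modelling work. No new data, visits or subjects are needed.

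### The trial is a 2x2 crossover, but no stated analysis is a within-subject laser-versus-sham contrast, and the between-group effect used to size it compares treatment sequences

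*Protocol article*

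**What the plan says.** **Design.** In the Study design section, "the subject will be randomly assigned to 1 of 2 groups in a ratio of 1:1". After 8 weeks of treatment and a 2-week washout, "the control group will switch to the experimental group while the experimental group will switch to the control group". The randomised groups are therefore the two sequences, laser then sham and sham then laser.

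**Outcome.** From the Outcome assessment section: "The primary outcome measurement is the BMI change from baseline". The section does not say whether baseline is the start of the trial or the start of each period.

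**Analysis.** The Statistical analysis section names three inferential methods:

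- An unpaired Student's t-test that sets one group against the other.
- Paired t-tests over time, described as follows: "The difference of evaluation scores before and after each examination point will be analyzed using paired" tests.
- A repeated-measures ANOVA, run "across the 8 data collection points (treatments for 16 weeks, followed-up evaluation biweekly".

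**Sample size.** The Sample size section uses G*Power's between-factors test for repeated measures with effect size 0.25, alpha 0.05, power 0.80, 8 measurements and correlation 0.2. It reports a minimum of 92 subjects, raised to 104 (52 per group) for 10% drop-out.

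**The concern.** A crossover earns its efficiency by comparing the two treatments within the same person. The only paired test in the plan compares before with after, which is an uncontrolled time comparison. The two methods that involve groups are parallel-group methods, and their meaning depends on what a group is once everyone has switched.

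The 8 measurements in the sample size calculation match the 8 collection points of the ANOVA. The natural inference is that the ANOVA's between-group main effect is meant as the treatment test. In a crossover that effect sets one sequence against the other, and each sequence contains equal amounts of laser and sham. A trial analysed that way would very probably report no difference even if laser worked.

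**Working it through.** **1. The plan's own figure.** For the between-group effect, lambda = f² × N × m / (1 + (m − 1) × rho). With f = 0.25, N = 92, m = 8 and rho = 0.2, lambda = 0.0625 × 92 × 8 / 2.4 = 19.17. This gives 99.1% power, not 80%. Power of 80% needs N = 40. The stated 92 is reached only at rho of about 0.66 to 0.67. The drop-out step is consistent: 92 / 0.9 = 102.2, so 103, or 104 for equal groups. That 92 cannot be reproduced is a separate matter. What counts here is which effect was powered.

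**2. Group = randomised sequence.** Sixteen treatment weeks with biweekly visits give 8 points, 4 per period. Let the laser effect be d, with no carryover.

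- Laser-then-sham mean: (4d + 4 × 0) / 8 = d/2.
- Sham-then-laser mean: (4 × 0 + 4d) / 8 = d/2.
- Expected between-group difference: 0 for any d. A period effect common to both sequences also cancels.

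Simulation with 46 per sequence, d = 0.5 SD, rho = 0.2 and 4,000 runs:

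| Carryover (share of d) | Between-group estimate | Between-group rejection | Crossover-contrast estimate | Crossover-contrast rejection |
|---|---|---|---|---|
| 0 | 0.00 | 4.9% | 0.50 | about 100% |
| 50% | 0.13 | 20% | 0.38 | about 100% |
| 100% | 0.25 | 57% | 0.25 | 97% |

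If the effect builds up over each period without carryover, the between-group test still rejects in only 5.2% of runs. What it detects under carryover is the carryover itself.

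**3. Group = current treatment.** The t-test now sets 104 laser values against 104 sham values from the same people. The unpaired standard error exceeds the correct one by the factor 1 / sqrt(1 − r), where r is the within-person correlation of the analysed variable. Assume visit-to-visit SD 0.8 and between-subject SD 3.5 kg/m², with compound symmetry. Neither SD is in the protocol.

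- *Change from each period's own baseline:* the errors are independent, so r = 0 and the factor is 1.0.
- *Change from one shared baseline:* the shared baseline error contributes 0.64 of a variance of 1.28, so r = 0.5 and the factor is 1.4.
- *Raw BMI:* r = 12.25 / 12.89 = 0.95, and the factor is sqrt(12.89 / 0.64) = 4.5.

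Power at a true effect of 0.5 kg/m² with 52 per sequence:

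- Unpaired test, own-period baselines: SE = sqrt(1.28 × 2 / 104) = 0.157, power about 89% (simulated 88%).
- Crossover contrast on end-of-period BMI: SE = sqrt(1.28 / 104) = 0.111, power about 99%.
- Unpaired test, shared baseline: simulated power 95% at 0.5, but it rejects in only 0.6% of runs when there is no effect, so it is strongly conservative.

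**4. Group-by-time interaction.** At each visit the sequence difference is +d in period 1 and −d in period 2. The interaction has (2 − 1) × (8 − 1) = 7 df, and lambda = (52 / 2) × 8 × d² / 0.64.

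- d = 0.3: lambda = 29.25, power 99%.
- d = 0.5: lambda = 81.25, power about 100%.
- d = 0: simulated rejection about 5%, with or without a common period shift of 1 kg/m².

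A common period shift goes into the time main effect and leaves the interaction untouched.

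**The case against.** The Study design section also uses group for the treatment currently received: it names the groups by laser and sham and has subjects move from one to the other. On that vocabulary the t-test compares laser with sham and nothing cancels. The analysis section never says that the ANOVA's between-group main effect is the treatment test. The interaction in the same ANOVA would detect a laser effect, and a t-test confined to the first period would be a valid randomised comparison (power 97% at rho 0.2 and 73% at rho 0.8, for d = 0.5 SD and 46 per sequence). Period terms, random effects and covariates may sit in an analysis plan that is not shown.

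Most of this stands, and it limits the point. A reader might infer that the trial cannot answer its own question, that the interaction is confounded with period, or that the t-test's standard error is always inflated severalfold. The documents support none of these. Sequence cancellation depends on one reading, the interaction is free of common period effects, and the primary outcome is a change score, for which the loss ranges from nothing to about 1.4-fold in the standard error.

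What does not stand is that this is mere missing detail. The article commits to named tests, and it sizes the trial on the between-group effect with 8 measurements. An analysis plan would have to contradict these statements, not just fill them in.

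**Conclusion.** The point holds. No analysis stated for this crossover is a within-subject laser-versus-sham contrast. The only effect tied to the sample size is the between-group one, which without carryover has expectation 0 and rejects at alpha whatever the laser effect. If group means current treatment, the t-test is usable but ignores the pairing: near-correct for own-period change, conservative for a shared baseline, more so for raw BMI. The interaction carries the treatment effect, but as an unnamed omnibus test without an estimate.

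Exact cancellation assumes no carryover, which is what the washout aims for. The standard-error and power figures rest on the assumed SDs and on compound symmetry. The plan should be corrected before analysis, because the choice among these readings decides whether a real effect is visible.

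**What to change.** **Statistical analysis section.** Name one primary analysis: a crossover model of BMI change, or of end-of-period BMI with that period's baseline as covariate. Use fixed effects for treatment, period and sequence and a random subject effect. State which baseline defines the change, so that the model matches the primary outcome. Report the laser-minus-sham difference with its 95% CI. Keep the biweekly measurements as a treatment-by-week description within period.

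**Sample size section.** Restate the justification for this within-subject contrast at the planned 104 subjects, with the assumed within-person SD of the outcome. No further enrolment is needed.

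**Cost.** Two reworded sections and one new calculation, with no new data or visits. The model does not remove carryover: the table shows its estimate also shrinks when carryover is present, so the result still depends on the washout.

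### One P < 0.05 rule covers between-group tests, before/after tests and an ANOVA, and no named test or time point decides the primary BMI question

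*Protocol article*

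**What the plan says.** All references are to the protocol article.

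- **Outcome assessment:** "The primary outcome measurement is the BMI change from baseline". No visit or crossover period is given. Assessments take place before the trial, every 2 weeks on treatment, and 2 months after the last treatment.
- **Statistical analysis, test 1:** after means and SDs are calculated, "the evaluation between the two groups will be compared using a" Student's t-test. The sentence names no visits.
- **Statistical analysis, test 2:** "The difference of evaluation scores before and after each examination point will be analyzed using paired" t-tests.
- **Statistical analysis, test 3:** a repeated measures ANOVA for "longitudinal and repeated measured data for the clinical indices across the 8 data collection points". The effect of interest (group, time or group by time) is not named.
- **Statistical analysis, threshold:** a P value below 0.05 "will be regarded as statistically significant for the above statistical analyses".
- **Sample size:** based on a "repeated measures between factors design to show a significant difference", with "effect size = 0.25; α = 0.05; 1 – β = 0.8" and "number of measurements = 8; correlation among repeated measures = 0.2". The Statistical analysis section does not carry this over as the main test.

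**The concern.** The three kinds of test answer different questions but stand on an equal footing. Only a comparison between laser and sham bears on the trial's question. A before/after test within one arm also picks up placebo response, time trend and regression to the mean. The last of these is plausible here because subjects are selected for BMI over 25 kg/m² and attend 3 times a week. The trial was set up with a sham control to remove such effects, and a significant before/after result reported on the same footing would bring them back.

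Because the primary outcome is tied to no time point and no test, several results could also be put forward as the primary BMI finding once the data are known.

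**Working it through.** **1. Does the Sample size section settle the primary test?** The stated inputs are f = 0.25, m = 8, ρ = 0.2, α = 0.05, power 0.80 and, from the design, 2 groups. For the between-factors test, λ = N f² m / (1 + (m − 1)ρ), with 1 and N − 2 df.

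- Here λ = N × 0.0625 × 8 / 2.4 = 0.2083 N.
- N = 40 gives λ = 8.33 and power 0.80. The stated minimum of 92 gives λ = 19.17 and power 0.99.

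The stated 92 is therefore not reproduced from the stated inputs. That is a separate matter. It matters here only because the calculation cannot be used to work backwards to a single intended primary test.

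**2. Before/after tests when laser does nothing.** Suppose both arms drift by d. The paired t statistic is then noncentral t with n − 1 df and noncentrality d / (SD/√n). The protocol gives neither d nor SD, so both are assumptions, in kg/m². n = 52 is one randomised group. n = 104 is all subjects under laser with both sequences pooled and no drop-out. The entries are the probability of two-sided P < 0.05:

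| n | SD of change | d = 0.1 | d = 0.2 | d = 0.3 |
|---|---|---|---|---|
| 52 | 0.8 | 14% | 42% | 76% |
| 52 | 1.2 | 9% | 22% | 42% |
| 104 | 0.8 | 24% | 71% | 97% |
| 104 | 1.2 | 13% | 39% | 71% |

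Example: d = 0.2, SD = 0.8, n = 104 gives noncentrality 0.2 / (0.8/10.198) = 2.55. Against a critical value of 1.983, the probability is 0.71.

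These rates are for a single before/after test. The plan has one at each examination point.

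**3. Between-group tests if run at every visit.** This is a conditional reading. Two-weekly visits give 8/2 = 4 per treatment period and 8 over the 16 treatment weeks. Treat the k test statistics as equicorrelated standard normals with correlation r. The chance of at least one |Z| > 1.96 with no effect is:

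| r | 4 visits | 8 visits |
|---|---|---|
| 0.5 | 16% | 25% |
| 0.8 | 11% | 16% |
| 0.9 | 9% | 12% |
| 0.95 | 8% | 10% |

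The range starts at r = 0.5 because every change score subtracts the same baseline. Under compound symmetry, Var(Yj − Y0) = 2σ²(1 − ρ) and Cov(Yj − Y0, Yk − Y0) = σ²(1 − ρ). The correlation of the changes is therefore 0.5 whatever ρ is. Values above 0.5 allow for BMI at neighbouring visits tracking more closely than that model implies.

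**4. Cross-check and comparison with one named test.** A null simulation used 46 per arm, a baseline plus 8 later visits, compound symmetry with ρ of 0.2, 0.8 or 0.95, and a parallel comparison. It gave about 25% for any of 8 between-group t-tests on change, in agreement with step 3. A single pre-named t-test at the last visit gave 4.8% to 5.2%.

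**The case against.** The strongest reply is that P < 0.05 is only a nominal threshold. Nowhere does the article say that any one significant result proves efficacy, or that a before/after fall counts as a laser effect. The Sample size section frames efficacy as real against sham treatment and sizes the trial on one between-group analysis, which hints at a main test. A condensed article may leave test ordering to a fuller plan, and the trial is called a pilot that will inform larger ones.

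Much of this stands. A reader might infer that the trial will declare laser effective on any significant test. The text does not say so, and the rates in step 3 depend on that reading. They also assume between-group tests at each visit, whereas the wording about examination points attaches only to the paired tests. A reader might also take the planning correlation of 0.2 and obtain 18% over 4 visits and 32% over 8. That correlation is for raw measures, and the shared baseline rules it out for change scores under compound symmetry. Nor does the text say that the t-test uses raw values instead of changes.

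What does not stand is that this is only missing detail. The article affirmatively gives all three kinds of test the same threshold, and a fuller plan that named one would have to override that sentence. The sample-size hint gets no priority in the Statistical analysis section. The pilot label softens the consequence, but the stated aim is still to assess effectiveness.

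**Conclusion.** The point holds as a badly fixed rule: equal P < 0.05 standing for tests that do and do not compare laser with sham, and no deciding test or time point for BMI change.

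The firm part is qualitative: the paired tests cannot separate laser from sham. Their false-alarm rate of about 9% to 76% at n = 52 and 13% to 97% at n = 104 rests on assumed drift and SD. Common drift is plausible, but nothing in the document shows that it will occur.

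The between-group inflation, about 8% to 16% over 4 visits and 10% to 25% over 8, is conditional on a per-visit, any-one-counts reading. It should not be presented as the trial's false-positive rate. This is a cheap improvement, not a flaw that invalidates the design.

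**What to change.** In the Statistical analysis section:

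- Name one primary test: the laser-sham difference in BMI change from period baseline to the end of the 8-week treatment period, two-sided at 0.05. Estimate it within subject across both crossover periods, with a period term and baseline adjustment.
- Report other visits and outcomes as supportive estimates with 95% confidence intervals.
- State that the before/after paired tests are descriptive and support no efficacy claim.

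The cost is two or three sentences and fewer nominally significant results to report. The article does not say plainly whether BMI is recorded at the start of the second period. If it is not, one measurement at that visit is needed as the period baseline.
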